### Procedures, recruitment and randomization

Eligible women will be identified by the participating hospital. Referring healthcare providers will be contacted to ensure timely referral (< 14 + 0 weeks’ GA). Women eligible for the trial will be counseled before participation by medical doctors or research nurses in accordance to the ‘Good Clinical Practice (GCP)’ guidelines [30]. Written informed consent will be obtained (Supplement 1 and 2).

Following participation, the participant will be entered in a web-based computerized database (ALEA®) for randomization. After complete registration in the online randomization database, the allocation will be shown. The online randomization software is available at all times. Randomization will be performed using block randomization with random block samples of *N* = 4–16. Due to the nature of the intervention, this will not be a blinded study.

### Control group

In the control group, participants will receive ‘care as usual’ which consists of a viability and pregnancy dating ultrasound examination around 10 weeks’ gestation followed by counseling for aneuploidy testing. Aneuploidy testing will be performed either via the first trimester combined test or via non-invasive prenatal testing (NIPT). Furthermore, an advanced ultrasound examination between 18 and 22 weeks’ gestation will be performed to screen for fetal anomalies. When indicated, additional ultrasound examinations will be planned, for instance fetal cardiac evaluation with a pediatric cardiologist.

### Intervention group

The intervention consists of a first trimester 2D and 3D VR ultrasound examination between 11 and 14 weeks GA. The examination will be performed on a Voluson E10 (GE Healthcare, Austria) using a 4–9 MHz or 6–13 MHz high frequency transvaginal transducer or 2–6 MHz transabdominal transducer. A complete ultrasound examination will take 30–45 min per fetus. Ultrasound examinations will be performed according to international guidelines on safe use of ultrasound in the first trimester of pregnancy and as such, total scanning time will be kept as low as possible (ALARA-principle) [31].

The ultrasound examination will be performed by two examiners (examiner A and B) unable to see of each other’s results. Examiner A will perform the 2D ultrasound and (2D) evaluation of fetal organ structures using a protocol with standard anatomical views and measurements (Supplement 3). The cardiac examination, based on international ISUOG practice guidelines, is expanded with at least 7 measurements or planes: four chamber view with and without color Doppler, left outflow tract with color Doppler, right outflow tract with color Doppler, three vessel view, trachea view, tricuspid valve pulsed wave Doppler and a measurement of cardiac axis [32]. By default a transvaginal ultrasound examination will be performed. Only if fetal structures cannot be sufficiently visualized or if a women objects to a transvaginal examination, a transabdominal approach will be performed. During the 2D ultrasound examination, in addition to the already described 3D ultrasound datasets, four-dimensional spatio-temporal image correlation (4D STIC) datasets of the fetal heart will be acquired. Examiner B will evaluate the acquired 3D volumes using the 3D VR Desktop system [18]. Participants undergoing the first trimester scan will be unable to see the 2D scan. This is necessary to test their experience and objective reaction with respect to the 3D VR images. Thus, the influence of 3D VR ‘holograms’ on future parents’ perception can be investigated and compared to their 2D ultrasound experience later in pregnancy (at 20 weeks).

The 3D VR images will be extensively discussed with the future parents: this will take 30 min. At the end of the 3D VR evaluation and discussion, examiners A and B will compare their findings to reach agreement. In case of an anomaly, participants will be informed about the presence or suspicion of malformations by examiner B. Routine care will then be offered, consisting of an advanced anomaly scan by an experienced and independent sonographer.

In the absence of an anomaly, the intervention group will undergo a routine second trimester 2D ultrasound scan as part of ‘care as usual’.

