### Virtual reality examination

The 3D VR Desktop provides a user-friendly possibility to interact with the ‘hologram’ and measure distances and semi-automatic volumes of different structures [16]. The desktop is equipped with a wireless joystick to manipulate the 3D volumes. A ‘hologram’ of the 3D volume is created using the V-Scope software (Erasmus MC, Rotterdam, The Netherlands). With stereoscopic glasses (similar to those used to watch a 3D movie) the examiners and patients (i.e. future parents) are able to perceive depth and to interact with the volume in all three dimensions. The ideal viewing angle or cutting plane can be obtained by turning, enlarging and clipping the 3D volume. The 3D VR examination will be performed using the same protocol with standard anatomical views and measurements (Supplement 3).

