### Outcome measurements

The primary outcome will be the detection rate of fetal anomalies using first trimester 3D VR ultrasound in addition to the second trimester 2D ultrasound in a high risk population. Neonatal or histopathological examinations are considered the gold standard for the detection of congenital anomalies. For the detection rate analysis the sensitivity, specificity, positive and negative predictive values will be calculated for all ultrasound techniques for first trimester examination (i.e. 2D and 3D VR) in the intervention group and second trimester 2D examination in both groups (control group as well as intervention group). The detection rate of both first trimester examinations (i.e. 2D and 3D VR) will be compared. The detection rate of first trimester 2D will also be compared to the second trimester 2D ultrasound in the intervention group. In addition, we will assess the performance of the first trimester anomaly 2D and 3D VR ultrasound and the additional findings of the subsequent second trimester 2D ultrasound to gain a better insight into the whole diagnostic process.

The diagnostic performance of the first trimester ultrasound examination protocol will be compared to international ultrasound guidelines. Anatomical views (i.e. sagittal, transversal) according to our standardized protocol acquired per fetal structure will be evaluated as satisfactory or unsatisfactory. This assessment will be used to evaluate image quality per fetal structure and per modality, i.e. first trimester 2D and 3D VR. By doing this we will be able to examine the anatomical views which are essential to be included in the protocol, and the ones which are not. This evaluation will lead to optimization of the examination protocol in the future.

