### Statistical issues

#### Sample size

The prevalence of anomalies in the high risk group is 5–10% [38, 39]. The detection rate for fetal anomalies with 2D ultrasound in the first trimester lies between 18.2 and 71.8% [7]. As mentioned before, the detection rate in a high risk population is estimated at 61%, and in a low risk population at 63% for 2D ultrasonography [6, 8]. The detection rate for anomalies of the first trimester 3D VR ultrasound is 62.5% [20]. For second trimester (18–22 weeks’ gestation) 2D ultrasound the detection rate lies between 44.3 and 74.4% [40–42].

For sample size calculation with a superiority analysis we assumed a 65% detection rate for a second trimester 2D ultrasound examination and a 70% detection rate for the combined detection of first trimester 3D VR and second trimester 2D ultrasound examination in a high risk population. With an assumed prevalence of 7.5% and an alpha-error of 0.05 with a desired power of 0.80, a total group of *N* = 2800 is required.

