This study will provide the highest level of evidence in the evaluation of first trimester 3D VR ultrasonograhpy in a high risk population concerning quality of life and cost-effectiveness. Only with a randomized controlled trial, like this study, the additional value of the 3D VR desktop can be examined in terms of improved diagnostic yield of regular first trimester 2D ultrasound and patients perspectives. If this new modality proves to be cost-effective or shows to improve quality of life, it should be offered in addition to the second trimester 2D ultrasound examination. The wider implications of the results will give policymakers and healthcare professionals an educated choice as whether to add first trimester ultrasound for detection of congenital anomalies in a high risk group as part of routine care.

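### The added yield of 3D VR over first trimester 2D cannot be separated from the gain of a second independent reader, so the Discussion claims more for VR than the design can show

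*Protocol article*

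**What the plan says.** The section Intervention group sets up two readings per first trimester examination: "The ultrasound examination will be performed by two examiners (examiner A and B"), each without sight of the other's results. The roles are then fixed by modality. For 2D: "Examiner A will perform the 2D ultrasound and (2D) evaluation of fetal organ structures". For VR: "Examiner B will evaluate the acquired 3D volumes using the 3D VR Desktop system".

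The section Virtual reality examination holds the checklist constant: "The 3D VR examination will be performed using the same protocol with standard anatomical views and measurements". After both readings, "examiners A and B will compare their findings to reach agreement".

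Two uses of these readings are announced.

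- **Head-to-head and combined performance (Outcome measurements).** The head-to-head is: "The detection rate of both first trimester examinations (i.e. 2D and 3D VR) will be compared". The same section also plans to assess how first trimester 2D and VR perform and what the second trimester scan adds.
- **Added value of VR (Discussion).** The trial is presented as the design through which "the additional value of the 3D VR desktop can be examined in terms of improved diagnostic yield of regular first trimester 2D ultrasound".

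The control arm has a viability and dating scan but no first trimester anomaly scan. The article describes no arm or subset with first trimester 2D alone, no second 2D reading, and no VR reading by the person who read the 2D scan.

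**The concern.** A second masked reader will usually find some anomalies that the first one missed, even with the same technique. Here the second reader is always the VR reader. When B reports a true anomaly that A did not, the data cannot say whether VR showed it or whether another pair of eyes was enough. Randomisation does not help, because the arms differ by the whole first trimester package (2D, VR and two readers) and not by VR alone.

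What is at stake is the conclusion about the VR desktop itself. If the anomalies found by A or B, less those found by A alone, are reported as the yield of VR, a department could buy the equipment for a gain that a second 2D reader might also have given.

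**Working it through.** **Which comparisons contain the second reader**

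| Comparison | Readers on each side | What the difference contains |
|---|---|---|
| A's 2D rate against B's VR rate (Outcome measurements) | one against one | modality effect plus any average skill difference between those filling the roles |
| A or B, or their consensus, against A alone (the added yield in the Discussion) | two against one | VR effect plus second-reader gain |
| Intervention arm against control arm (primary) | whole strategies | effect of the whole first trimester package, including both readers |

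Only the second row carries the problem.

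**How large a second-reader gain could be**

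The article gives no figure for this gain, so there is none to reproduce. What follows is an illustration.

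*Inputs.*
- Sensitivity p. The section Sample size says of first trimester 2D that "the detection rate in a high risk population is estimated at 61" per cent, and gives 62.5% for first trimester 3D VR. I take 62% for both readers, which lies between the two and builds in no VR effect.
- Correlation φ between the two readings among affected fetuses. This is an assumption, shown as a range. The agreement above 0.99 in the Background concerns measurements, not detection of anomalies.
- Rule: a finding by either reader counts as detection. Consensus between A and B could retain less.

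*Formulae.* P(both detect) = p² + φ·p(1−p). Gain from the second reader = p − P(both detect) = p(1−p)(1−φ).

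*Numbers.* p(1−p) = 0.62 × 0.38 = 0.2356.

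| Assumed φ | Gain = 0.2356 × (1−φ) | Points |
|---|---|---|
| 0.9 | 0.0236 | 2.4 |
| 0.8 | 0.0471 | 4.7 |
| 0.7 | 0.0707 | 7.1 |
| 0.6 | 0.0942 | 9.4 |

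At φ = 1 the gain is zero.

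**The same check with the article's two first trimester rates**

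Let A read 2D at 61% and B read VR at 62.5%. P(both) = 0.61 × 0.625 + φ·√(0.61 × 0.39 × 0.625 × 0.375), and the gain over A alone is 0.625 − P(both).

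- φ = 0.9: the gain is 3.1 points. A second 2D reader at 61% would give 0.61 × 0.39 × 0.1 = 2.4 points.
- φ = 0.75: the gain is 6.7 points. A second 2D reader would give 0.61 × 0.39 × 0.25 = 6.0 points.

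If the correlation is the same for a 2D and a VR second reader (also an assumption), most of the apparent added yield in these examples would have come from any second reader. A VR reading that finds different kinds of anomaly would have a lower φ and a larger gain. The design has no 2D-plus-2D reading against which to recognise that.

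**The case against.** The strongest points on the other side are these.

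- **Two masked readers is a defensible design.** Having one person read both modalities would let the first reading influence the second. This stands; the masking is a strength, and the point is about what may be concluded from it.
- **A and B are roles, not people.** A reader might infer that modality is tied to particular staff. The article does not say so. The section Quality describes a group of trained sonographers, and who fills which role may be set out in the full protocol. This stands, and a skill imbalance is therefore only a possibility. Rotating staff would even out skill but would leave the second-reader gain in the added yield.
- **The planned head-to-head is clean of this gain.** A reader might infer that the 2D versus VR comparison is inflated by double reading. It is not, since it sets one reader against one reader.
- **The 5-point effect is a different quantity.** It is tempting to set 2.4 to 9.4 points beside the 65% against 70% of the sample size and conclude that double reading could explain the whole planned effect. The documents do not support that. The planned effect is between arms after the second trimester scan, and some anomalies found only by B would be found at that scan anyway.
- **B reads volumes acquired in the same session.** Shared acquisition and image quality would tend to raise φ and push the gain toward the low end. This is fair, but the documents give nothing with which to place φ.
- **The claim is a Discussion sentence, not an analysis rule.** True, but it states what the trial will be able to show, and the reporting would naturally follow it.

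**Conclusion.** The point holds for the added yield of VR over first trimester 2D, as claimed in the Discussion, and for the combined first trimester performance in Outcome measurements if that is credited to VR. As described, those quantities mix VR with a second independent reader. In the illustration the reader part is 2.4 to 9.4 points within the first trimester. This assumes equal readers at 62%, either reading counting as detection, and φ from 0.9 to 0.6; it shrinks toward zero as φ approaches 1.

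It does not hold against the paired 2D versus VR comparison, whose only risk here is a skill difference if the same staff tend to fill the same role. Nor does it hold against the primary between-arm contrast, which remains a valid test of the whole package but does not isolate VR.

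**What to change.** 1. **Restrict the claim.** Reword the Discussion sentence so that statements about VR itself rest on the paired comparison of A alone against B alone, using the readings recorded before A and B confer.
2. **Label the combined gain.** Report anomalies found by A or B, beyond those found by A, as the gain of 'second reader plus VR'.
3. **Balance and record the readers.** Where both examiners present are trained in both roles, draw roles A and B at random for each session, log the examiner for each reading, and include examiner as a factor in the paired analysis. If the full protocol already rotates staff, state that.

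The cost is a sentence of rewording, a role draw per session and a recorded field. No arm and no sample size changes. The small downside is that sonographers must be able to take both roles. Step 3 deals with skill differences only; it does not remove the second-reader gain, which is why steps 1 and 2 are needed as well. Isolating VR's incremental yield would take a second masked 2D reading, at least in a subset. That is a larger change and is not needed if the claim is restricted.

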### Virtual reality examination

The 3D VR Desktop provides a user-friendly possibility to interact with the ‘hologram’ and measure distances and semi-automatic volumes of different structures [16]. The desktop is equipped with a wireless joystick to manipulate the 3D volumes. A ‘hologram’ of the 3D volume is created using the V-Scope software (Erasmus MC, Rotterdam, The Netherlands). With stereoscopic glasses (similar to those used to watch a 3D movie) the examiners and patients (i.e. future parents) are able to perceive depth and to interact with the volume in all three dimensions. The ideal viewing angle or cutting plane can be obtained by turning, enlarging and clipping the 3D volume. The 3D VR examination will be performed using the same protocol with standard anatomical views and measurements (Supplement 3).

### Questionnaires

All participants will fill out questionnaires on health related quality of life. The following validated questionnaires will be sent at fixed time points in pregnancy: the MOS 36-item Short Form Health Survey (SF-36), the Hospital Anxiety and Depression Scale (HADS), the Spielberger State-Trait Anxiety Inventory (STAI) and a visual analogue scale (VAS) for wellbeing [33–35]. The four questionnaires will be sent digitally to the participants on the day of inclusion, the first trimester 3D VR ultrasound (or after 13 weeks GA for the control group), the second trimester 2D ultrasound and 4 weeks after the estimated due date, respectively. The answers will be recorded on a secure webserver on the Erasmus MC premises.

Direct healthcare costs will be recorded using the iMTA Medical Consumption Questionnaire (iMTA MCQ) [36]. All significant costs and health effects on the short term up to 4–6 weeks after delivery or termination of pregnancy will be considered. Therefore, these questionnaires will be sent at 20 and 32 weeks GA and 4 weeks after the estimated due date. In case of an intra-uterine fetal demise or termination of pregnancy during the trial, women will be sent specifically adjusted questionnaires.

Participant perspective on the 3D VR ultrasound will be evaluated with an in-house developed questionnaire. This survey includes questions about the value of ultrasound imaging in the first trimester and personal perception of the added value of 3D VR. This questionnaire will be sent after the first trimester 3D VR ultrasound or around 13 weeks GA in the control group. This questionnaire will be validated in a subset of 50 participants.

Ultrasonographer opinion of both the first trimester 2D and the 3D VR ultrasound will be evaluated by another in-house developed questionnaire. More specifically, the additional value of the 3D VR in terms of patient understanding, counseling and detection of anomalies will be examined.

### Follow-up

Baseline characteristics will be extracted from the electronic medical records and stored in a secured database. Only a select group of staff will have access to participant characteristics to ensure patient confidentiality.

Hospital or midwifery charts will be obtained to complete follow-up on neonates. In case of a fetal anomaly, additional information will be obtained, such as genetic testing or autopsy results.

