Secondary outcome measures will be health-related quality of life and cost-effectiveness of first trimester 3D VR ultrasound from a societal perspective. Health related quality of life will be expressed in physical, emotional and social functioning. Quality Adjusted Life Years (QALY’s) will be calculated from a maternal perspective, derived from the validated questionnaires. Actual expenses during the study will be measured using the standard costs as stated by the Dutch costing guidelines [37]. For each strategy (control versus intervention) the quality of life will be computed as well as the average costs per patient. The incremental cost-effectiveness ratio (ICER) will be calculated by dividing the difference in costs by the difference in quality of life. It represents the extra costs required to obtain one QALY. Furthermore, the cost per anomaly detected will be estimated. The cost-effectiveness analysis will span a period from approximately 8 weeks of gestation, when regular obstetric care starts, up to approximately 2 months beyond the estimated date of delivery. In this analysis, costs and effects will not be discounted due to a short time frame. Indirect costs will not be accounted for. The costs will be presented in Euros. The index year will be 2018.

Additionally, through a newly implemented questionnaire, the perspective of both patient and ultrasonographers on the new 3D VR modality will be surveyed. The participant perspective of the first trimester 3D VR ultrasound group (=intervention) will be compared to second trimester 2D ultrasound (=control).

An overview of all patients’ characteristics and data is shown in Table 1.

**Table 1 Tab1:** Patient characteristics collected within the VR FETUS study. Details of data collection form the first trimester up to 6 weeks after delivery are depicted

**Maternal Characteristics**	**Outcome**
Age	Years (mean ± SD)
Ethnicity	Dutch/Other western/Non-western
Level of education	Low, middle, high
Postal code	
Medical history	Unremarkable/Diabetes/Epilepsy/Other
Obstetrical history	Parity, miscarriage, previous pregnancy with congenital anomaly
Family history	Unremarkable/family members with congenital anomaly
Marital status	Married/not married
Global household income	€0–20.000/€20.000–35.000/€35.000–65.000/>€65.000 annually
BMI	Kg/m^2^ (mean ± SD)
Alcohol use during first trimester	No/Yes: how many units per day?
Smoking during first trimester	No/yes: how many cigarettes per day

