Recreational drug use during first trimester	No/yes: what drugs; frequency per day?
Folic acid use during and/or prior to pregnancy	No/yes during pregnancy/yes started prior to pregnancy
Pregnant after artificial reproductive technology	No/yes: what type of assisted reproduction
First trimester screening for aneuploidy	No/yes: result
Medication	No/yes: what medication, dosage, starting and stopping date?
Antidepressant	Never/yes currently/yes previous use
**Questionnaires**	**Timing**
Current health status^a^	At inclusion, intervention or 13 weeks’ GA, 20 weeks’ GA, 6 weeks after due date
Anxiety and depression^b^	At inclusion, intervention or 13 weeks’ GA, 20 weeks’ GA, 6 weeks after due date
State and trait anxiety^c^	At inclusion, intervention or 13 weeks’ GA, 20 weeks’ GA, 6 weeks after due date
Current health status by VAS^d^	At inclusion, intervention or 13 weeks’ GA, 20 weeks’ GA, 6 weeks after due date
Medical consumption^e^	At 20 weeks’ GA, 32 weeks’ GA, 6 weeks after due date
Patient satisfaction with 3D VR	At intervention or 13 weeks’ GA, 6 weeks after due date
**Ultrasound**	**Measurements**
At inclusion, 1st trimester	Viability, CRL, multiple pregnancies, location
Intervention: 2D + 3D VR First Trimester Ultrasound, 1st trimester	Fetal anomaly scan using 2D and 3D VR. Growth parameters, detection of anomaly. See supplement A
Advanced fetal anomaly scan, 2nd trimester	Fetal anomaly scan using 2D. Growth parameters, detection of anomaly
**Pregnancy outcome**	**Outcome**
Outcome	Live birth, termination, intra-uterine fetal demise
Mode of delivery	Vaginal / Instrumental delivery / Cesarean section
Gestational age at delivery	Days (mean ± SD)
Invasive testing	No/yes: result
Date of invasive testing	
**Neonatal outcome**	**Outcome**
Birthweight	Birthweight, grams (mean ± SD)
Gender	Male/female
Congenital malformation	No/yes: what malformation
Prenatal diagnosis	Confirmed/discrepancy in findings: postnatal new or other findings

^a^SF-36: MOS 36-item Short Form Health Survey, ^b^HADS: Hospital Anxiety and Depression Scale, ^c^STAI: Spielberger State-Trait Anxiety Inventory, ^d^VAS: visual analogue scale, ^e^iMTA MCQ: iMTA Medical Consumption Questionnaire, CRL: Crown-Rump Length, 2D: two-dimensional, 3D VR: three-dimensional virtual reality

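### Uneven search for anomalies after birth: those missed by ultrasound and absent from routine charts count as unaffected, so detection rates may be overstated by an unknown amount

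*Protocol article*

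**What the plan says.** The Outcome measurements section sets the reference standard: "Neonatal or histopathological examinations are considered the gold standard for the detection of congenital anomalies". Sensitivity, specificity and both predictive values are to be calculated against it.

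The Follow-up section says where that information comes from. For all neonates: "Hospital or midwifery charts will be obtained to complete follow-up on neonates". Beyond the charts: "In case of a fetal anomaly, additional information will be obtained, such as genetic testing or autopsy results".

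Table 1 has two relevant neonatal items. Congenital malformation is recorded as "No/yes: what malformation". Prenatal diagnosis is recorded as "Confirmed/discrepancy in findings: postnatal new or other findings".

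The article gives several end points after birth:
- The Questionnaires section sends the final mailing 4 weeks after the estimated due date and counts costs and health effects up to 4–6 weeks after delivery or termination.
- Table 1 places the same final questionnaires 6 weeks after the due date, and its caption reads "Details of data collection form the first trimester up to 6 weeks after delivery are depicted".
- The cost-effectiveness analysis runs to about 2 months past the due date.

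None of these is named as the age at which an infant is classified as affected or unaffected.

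On blinding: "Due to the nature of the intervention, this will not be a blinded study". On planning rates: "we assumed a 65% detection rate for a second trimester 2D ultrasound examination", against 70% for the combined first and second trimester examinations.

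**The concern.** A detection rate is only as sound as its denominator, which is all affected fetuses, including those that ultrasound missed. Here the depth of the search depends on whether an anomaly has been recorded. A recorded anomaly leads to further records. An infant with no recorded anomaly rests on whatever routine care wrote in the chart by an age that is not fixed.

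An internal anomaly that ultrasound missed and that is not yet apparent is entered as no malformation. It should be a false negative but becomes a true negative. It leaves the sensitivity denominator and also improves the negative predictive value.

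The absolute rates matter as well as the difference between arms, because the Background says that the yield of 3D VR will be compared with international guidelines and literature.

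**Working it through.** **Inputs.** From the Sample size section: detection rate s = 0.65 (control) and 0.70 (intervention), prevalence 7.5%, N = 2800. Assumed: 1:1 allocation (the ratio is not stated) and one fetus per participant. Also assumed, because the documents give no value: the share u of prenatally missed anomalies that the charts also miss, shown from 0 to 40% and taken as equal in both arms.

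**The plan's own figure.** A two-sided 5% test of 65% against 70% with 80% power needs 1377 per arm, 2754 in total, which is close to 2800. These are anomaly cases. At 7.5% prevalence they correspond to 2754 / 0.075 = 36,720 participants. That is a separate matter; N is used below only to count expected cases.

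**Apparent sensitivity.** Detected anomalies stay in the denominator. Of the missed ones, only the fraction (1 − u) does:

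apparent rate = s / (s + (1 − s)(1 − u))

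| u (assumed) | Control | Intervention | Difference |
|---|---|---|---|
| 0 | 65.0% | 70.0% | 5.0 |
| 10% | 0.65/0.965 = 67.4% | 0.70/0.97 = 72.2% | 4.8 |
| 20% | 0.65/0.93 = 69.9% | 0.70/0.94 = 74.5% | 4.6 |
| 30% | 0.65/0.895 = 72.6% | 0.70/0.91 = 76.9% | 4.3 |
| 40% | 0.65/0.86 = 75.6% | 0.70/0.88 = 79.5% | 4.0 |

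The overstatement is 2.4 to 10.6 points in the control arm and 2.2 to 9.5 in the intervention arm.

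**In cases.** 1400 × 0.075 = 105 anomalies per arm. At u = 20%, the denominator loses 105 × 0.35 × 0.20 = 7.4 control cases and 105 × 0.30 × 0.20 = 6.3 intervention cases.

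**Negative predictive value, control arm.** With specificity set to 100% for simplicity, each 100 fetuses give 92.5 + 7.5 × 0.35 = 95.125 negatives. The true value is 1 − 2.625/95.125 = 97.2%. It appears as 1 − 2.3625/95.125 = 97.5% at u = 10% and 1 − 1.575/95.125 = 98.3% at u = 40%.

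**Opposite force.** Let v be the share of detected anomalies dropped as unconfirmed, for example a termination without histopathology. Then the apparent rate = s(1 − v) / (s(1 − v) + (1 − s)(1 − u)).
- u = 20%, v = 20%: 65% and 70%, so the two losses cancel.
- u = 0, v = 20%: 0.52/0.87 = 59.8% and 0.56/0.86 = 65.1%.

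**Scale for the comparison between arms.** With 105 anomalies per arm, the standard error of the difference is √(0.65 × 0.35/105 + 0.70 × 0.30/105) = 6.5 points, against a shift of 0.2 to 1.0 point.

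**The case against.** The strongest reply is that the article names one reference standard for everyone and obtains neonatal charts without restricting them to pregnancies with a positive scan. Genetic and autopsy results mainly characterise an anomaly or cover a fetal loss. Autopsy cannot apply to a surviving infant, so some difference in depth is unavoidable. All of this stands.

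A reader might infer more than the documents support:

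- *Extra records are sought only for anomalies known before birth.* The Follow-up sentence does not say so and does not exclude an anomaly first found in the neonate. On either reading, though, an anomaly that no chart records triggers no further request.
- *Missed anomalies drop out as a class.* They do not. Table 1 records malformations in neonates and has an entry for new postnatal findings, so a miss that reaches the chart remains a false negative. An anomaly missed in the first trimester but seen in the second also stays in.
- *Every detection rate is overstated.* This is not shown. The share u is undocumented and may be zero, and loss of unconfirmed detected cases lowers the rates.
- *The bias could create a false benefit.* With an equal share in both arms it slightly reduces the difference. In an unblinded trial the share could differ by arm, but the documents do not show that it does.

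It is also fair that a journal article condenses a fuller protocol. The absence here of a standard neonatal examination or an adjudication procedure is therefore not held against the plan. The point rests on what the article does state: a two-level rule for gathering information, and end points after birth that do not agree.

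**Conclusion.** The point holds in a limited form. Ascertainment is uneven, and the article fixes no common age of classification. Anomalies missed by ultrasound and also absent from the charts are counted as unaffected, which can overstate sensitivity and negative predictive value. For sensitivity the size is about 2 to 11 points if 10% to 40% of missed anomalies escape the charts, and zero if none do. That range is an assumption and not an estimate, and the net direction also depends on how detected but unconfirmed cases are handled.

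The effect on the comparison between arms is small: 5.0 points becomes 4.8 to 4.0 if the share is equal in both arms, well inside the sampling error. The absolute rates are more exposed. At an assumed 20%, the control rate rises by 4.9 points, about as much as the 5-point difference that the trial was planned around. This calls for an inexpensive improvement; it does not invalidate the design.

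**What to change.** 1. Add one item to the existing final questionnaire, for all liveborn infants in both arms, asking whether any congenital anomaly has been diagnosed or investigated since birth.
2. For each positive answer, and for each new postnatal finding in the charts, request the same additional records as for an anomaly detected prenatally.
3. Reconcile the 4-week timing in the Questionnaires section with the 6-week timing in Table 1, and classify every infant as affected or unaffected at that one age, whatever the scans showed.
4. State as a limitation that anomalies still silent at that age remain uncounted.

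The cost is one question in a mailing that already goes out, plus record requests for what should be few positive answers. The downsides are some non-response, which should be reported by arm because the trial is unblinded, and slightly lower reported detection rates. Self-report should prompt the record request and not decide the classification.
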